### Schedule of visits

Although this is a feasibility study focusing on recruitment, completion, adverse effects and acceptability (using a Likert questionnaire (online supplemental
appendix 1), our overarching research aims to explore the impact of dyspnoea in individuals by using the submaximal CWR^55 56^ at 80% of VO_2_ max to experimentally provoke dyspnoea symptoms and evaluate the effects of our proposed relieving techniques. According to the *American Thoracic Society 2019* standards,^57^ spirometry will be employed to evaluate pulmonary function, encompassing key parameters such as FEV1, FVC and FEV1/FVC. Basic vital signs, including oxygen saturation (SpO_2_), heart rate (HR), arterial blood pressure (BP), respiratory rate (RR) and temperature (T°), will also be measured to ensure the safety of the patients and to support the study. Subjective dyspnoea assessments will be carried out using the Borg scale (0–10) (online supplemental appendix 2),^58 59^ a 100 mm Visual Analogue Scale (VAS) for dyspnoea (online supplemental appendix 3) complemented by the mMRC dyspnoea scale for individuals with COPD (online supplemental appendix 4), the CAT questionnaire (online supplemental appendix 5), *St George’s Respiratory Questionnaire (SGRQ)* (online supplemental appendix 6) and the time to return to initial Borg Score serves as a measure of recovery following the exercise test. Data on rehabilitation performance will include measurements of workload, VO_2_ max, pedalling time and breathing and cardiac reserves. To confirm (yes or no) whether the baseline visit reached maximal effort at VO_2_ max, the criteria for maximal effort from the *European Respiratory Society (ERS) statement on the standardisation of cardiopulmonary exercise testing (CPET) in chronic lung diseases* will be applied*.*^60^ The quality of blinding with the proposed sham will also be assessed (online supplemental appendix 7). Other questions will assess participants’ expectations and perceived intervention efficacy during each exercise test using a Numeric Rating Scale (NRS) (online supplemental appendix 8). A short questionnaire will evaluate the anxiety, depression and catastrophisation related to breathlessness (online supplemental appendix 9). All the data expected to be collected are detailed in online supplemental
tables 1 and 2*.*

Throughout the entire duration of the study, participants’ complete medication regimen will be assessed, and their medication must remain stable during the trial. As part of the pulmonary rehabilitation programme, the eight participants will undergo a medically advised first CPET at VO_2_ max following the data measurement procedures of the study. The Borg scale will be evaluated before the test, every 3 min during the test and at the end of the test. For the baseline visit, only SpO_2_ will be measured before and after CPET. Additionally, spirometry parameters, including FEV1, FVC and FEV1/FVC, will be measured before the test. Data on rehabilitation performance, such as VO_2_ max, breathing and cardiac reserve and the assessment of maximal effort testing, will be useful for the setting of the next two visits. This baseline CWR is crucial as it sets the parameters for the next two experimental visits and as it accounts for the effects of adaptation to the physical test (learning effect), ensuring that any observed changes in subsequent tests are not merely due to physiological adaptations or normal variations that occur in every test conducted under this protocol.

At least 1 week later, at the beginning of this first experimental visit, demographic data and medical records (confirmed via data entry form), the SGRQ and the Psychological Components Questionnaire will be administered. At this point, participants will receive either a cervical or facial neurostimulator, delivering cervical tVNS or trigeminal TENS. Then, they will undergo a submaximal CWR at 80% of VO_2_ max, with the intervention or the sham, and with the same data measurement of the baseline CWR with the addition of more dyspnoea evaluation questionnaires. These include the Borg scale assessed every minute during the test, the mMRC and CAT questionnaires administered before the test, and the VAS recorded before and after CWR. Participants’ expectations regarding the efficacy of the intervention will be assessed at rest, both with and without stimulation. At the end of the protocol, stimulation and perceived efficacy will be evaluated to gather additional subjective data on relief perception and the quality of the sham. Additionally, the time taken to return to the initial Borg score at rest following CWR will be measured. Vital signs, including SpO_2_, HR, BP, RR and T° will also be monitored throughout the entire duration of the test (except BP and T° that are only assessed before CWR).

Within 2 weeks after the first experimental visit, those who received an intervention (tVNS or trigeminal TENS) will receive the sham, and those who received the sham will receive an intervention. This switch occurs according to the randomisation process of the cross-over group assignment (figure 1). They all undergo a final submaximal CWR, with data collected in the same sequence during the first experimental visit.

In case of technical issues or other concerns affecting the validity of the test or the data collected during one of the visits, an additional visit (W4) could be added after the last experimental visit. If this visit takes place, it will follow the same exercise testing and intervention protocols as the two preceding experimental visits.

If patients experience significant discomfort or adverse effects during the test or interventions, they should immediately inform the healthcare provider so that appropriate measures can be taken to reassure and manage the patient effectively, including possibly stopping the procedure if necessary. The exercise test termination criteria, established by the *American Thoracic Society*, will be followed to ensure participant safety.^56^ Otherwise, common short-term side effects will be assessed frequently, with a minimum of one evaluation at the end of each experimental visit using a standardised questionnaire designed for the interventions of the study. This approach aims to promptly identify and screen for any undesirable effects experienced by participants (online supplemental appendix 10).

Study visits will be completed before starting or before completing the 12-week rehabilitation programme, with a minimal interval to allow recovery after exercise testing while limiting external influences on exercise tolerance assessments. The schedule for data collection of each variable is detailed in online supplemental
table 3*.*

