**Trial registration number:**

NCT06985628.

STRENGTHS AND LIMITATIONS OF THIS STUDYThis is the first study to investigate neuromodulation for alleviating dyspnoea perception in patients with chronic respiratory disease.The small sample size and cross-over design are appropriate for a feasibility trial but introduce potential learning bias and limit the interpretation of the efficacy of the interventions.Dyspnoea perception is assessed only in severe chronic obstructive pulmonary disease patients, limiting generalisability and scales used, such as Borg and Visual Analogue Scale, may not fully reflect its complex neurological dimensions.The proposed sham procedure and sham-related questionnaire are not validated but were adapted from pain studies to assess the feasibility and blinding quality in this novel context.Although the non-invasive nature of the interventions limits the specificity of neural targeting, it offers a safe and practical foundation for testing this novel approach in standardised exercise conditions.

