**Figure 1 F1:**
[figure not shown]
Study design of the cross-over sham-controlled feasibility trial. Description of intervention arms: (1) TENSac (visit 2 active → visit 3 sham); (2) TENSsa (visit 2 sham → visit 3 active). (3) VNSac (visit 2 active → visit 3 sham). (4) VNSsa (visit 2 sham → visit 3 active). W-2, W0 and W2 are presented as an example of ‘plausible scheduling’. An interval of 1–2 weeks will be planned between visit 2 and visit 3, whereas no specific interval (*at least 1 week*) is required between visit 1 and visit 2. TENS, transcutaneous electrical nerve stimulation; tVNS, transcutaneous vagus nerve stimulation.

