#### Secondary feasibility assessment

Acceptability of this study procedures (CWR, TENS, tVNS, etc) assessed by Likert score at the end of the last visit.Recruitment results: percent of recruited patients on the target sample size (which is 2 × n=4), and on the number of patients approached for screening.Numerical and descriptive occurrence of adverse effects and undesirable events throughout the complete study period, as reported by the patients and investigated by the researchers.

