### Assignment of interventions

At visit 1, participants will be randomised, using randomisation function of REDCap, to one of four groups for subsequent study procedures: TENSac (visit 2 active → visit 3 sham) or TENSsa (visit 2 sham → visit 3 active), VNSac (visit 2 active → visit 3 sham) or VNSsa (visit 2 sham → visit 3 active), in a 1:1:1:1 ratio through the randomisation function of REDCap. A non-blinded investigator will run the randomisation and allocation process. Given our small sample size (n=8), no stratification will be applied for randomisation.

However, in a future randomised controlled trial, the randomisation should be minimised for FEV_1_ (<35% or ≥35% predicted), sex (one female participant (n=1) and one male participant (n=1), for a total of two participants per group arm (n=2) of the randomisation) and the number of severe exacerbations in the preceding 12 months (0 or ≥1 events).

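### The only repeat slot for an invalid visit comes after the last one and its condition is not named, so replacing an invalid first experimental visit reverses that patient's analysed order

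*Protocol article*

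**What the plan says.** The protocol article, Schedule of visits, provides for technical or other problems "affecting the validity of the test or the data collected during one of the visits". The wording covers either experimental visit. The remedy is that "an additional visit (W4) could be added after the last experimental visit". Of the content of W4 it says only that "it will follow the same exercise testing and intervention protocols as the two preceding experimental visits". Those two visits differ in exactly one planned respect, active or sham, and the sentence does not say which of the two W4 delivers. No repeat of the first experimental visit before the crossover is described. A restart from W0 is described only for an exacerbation (Participants).

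The order of conditions is what is randomised within each device. Assignment of interventions lists "TENSac (visit 2 active → visit 3 sham) or TENSsa (visit 2 sham → visit 3 active"), with the matching pair for VNS, "in a 1:1:1:1 ratio through the randomisation function of REDCap". The Secondary feasibility assessment gives the target as 2 × 4 patients. The Figure 1 legend adds: "An interval of 1–2 weeks will be planned between visit 2 and visit 3".

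On change over time, the strengths and limitations list says that the small sample and the crossover design "introduce potential learning bias". Schedule of visits allows the visits to be finished either before the 12-week rehabilitation programme starts or before it ends.

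**The concern.** In a two-period crossover, a trend across tests cancels from the active-sham comparison when equal numbers of patients take each order. With eight patients in four sequences there are two per order and device, so the balance depends on very few people.

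A repeat placed after the last visit preserves the order when the second experimental visit failed. It does not when the first one failed. If W4 then gives the first condition again, the patient's valid data are the second condition at visit 3 followed by the first condition at W4. A patient randomised to active then sham supplies sham-then-active data. The repeated condition is measured after one more test than its comparator and, if the patient is already in rehabilitation, after more training.

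At stake are the exploratory active-sham contrasts in Borg score and pedalling time. The repeat rule could also be carried into the larger trial that this study is meant to prepare.

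**Working it through.** The article states no drift, power or period calculation, so there is no figure of its own to reproduce. The check is bookkeeping of test order.

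**Inputs from the article**
- Patients: 2 × 4 = 8. At 1:1:1:1, 8/4 = 2 per sequence, so each device has 2 active-first and 2 sham-first patients.
- Comparison: paired t-tests with and without the intervention (Statistical analyses). No order term is mentioned there.
- Reference size: MCID of 1 for the maximum Borg score (Exploratory outcomes). That outcome is a change from baseline, but the baseline is common to both of a patient's periods and cancels in active minus sham.

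**Assumptions**
- g1 is the drift from W0 to visit 3, and g2 the drift from visit 3 to W4. Neither is given in the article.
- The true effect is set to zero, so whatever remains is bias.
- W4 repeats the condition of the failed visit.
- The failed visit still counts as a test exposure.

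**Each patient's active minus sham difference**
- Active-first, no repeat: 0 − g1 = −g1
- Sham-first, no repeat: g1 − 0 = +g1
- Active-first, W0 invalid and repeated at W4: (g1 + g2) − g1 = +g2
- Sham-first, W0 invalid and repeated at W4: g1 − (g1 + g2) = −g2
- Active-first, visit 3 invalid and repeated at W4: 0 − (g1 + g2) = −(g1 + g2)

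**Mean over the four patients of one device**
- No repeat: (−g1 − g1 + g1 + g1)/4 = 0
- One active-first W0 repeated at W4: (g2 − g1 + g1 + g1)/4 = +(g1 + g2)/4
- One sham-first W0 repeated at W4: (−g1 − g1 + g1 − g2)/4 = −(g1 + g2)/4
- One active-first visit 3 repeated at W4: (−g1 − g2 − g1 + g1 + g1)/4 = −g2/4

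Over all eight patients, with the other device balanced, each value is halved.

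**Numbers with g1 = g2 = g (sizes, in Borg points)**

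| g | W0 repeated at W4, one device | same, all 8 | visit 3 repeated at W4, one device |
|---|---|---|---|
| 0.25 | 0.125 | 0.0625 | 0.0625 |
| 0.5 | 0.25 | 0.125 | 0.125 |
| 1 | 0.5 | 0.25 | 0.25 |

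If drift stops after visit 3 (g2 = 0), the first column falls to g1/4, which is 0.25 for g1 = 1.

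**Repeating W0 before crossing over instead.** The failed W0, its repeat and visit 3 are now tests one, two and three. The active-first patient contributes g1 − (g1 + g2) = −g2, and the device mean is (−g2 − g1 + g1 + g1)/4 = (g1 − g2)/4. This is zero when the drifts are equal. When both drifts have the same sign it is never larger than (g1 + g2)/4, and it matches it when g2 = 0.

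**The case against.** The strongest reply is that this is an optional visit in a feasibility study of eight people. The primary outcome is completion, the active-sham contrasts are exploratory, and the article says the study is not designed to determine efficacy and concedes learning bias. A contingency touching one patient cannot change the main conclusion. That stands, and it sets the weight of the point.

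Second, the article is condensed, so the condition given at W4 may be named in the full protocol. That is possible. The placement of the repeat, however, is stated here, and the order problem follows from the placement.

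Third, the article says the baseline test accounts for learning, requires stable medication and seeks to limit outside influences on exercise tolerance. These measures reduce drift but need not remove it. The baseline test is described as a maximal test with Borg readings every 3 min, although it is later called a baseline CWR. The experimental tests are submaximal with readings every minute. On that description W0 is the first exposure to the test being compared.

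A reader might also infer more than the text supports:
- *That the repeated condition alone gains from practice.* Visit 3 also follows the baseline test and W0; W4 adds one further exposure and more elapsed time.
- *That W4 always carries a rehabilitation gain.* All visits may be completed before the programme starts.
- *That the analysis will adjust in the wrong direction.* Statistical analyses states no adjustment by randomised sequence, so this would arise only if one were added using the randomised label.
- *That a bias of 0.5 Borg point is to be expected.* It needs a drift of a full MCID at each step, for which the article gives no support.

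**Conclusion.** The point holds as a minor design weakness with a cheap remedy. The single repeat slot reverses the analysed order of any patient whose first experimental visit is replaced at W4, and the article does not say which condition W4 delivers.

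One such patient biases that device's mean active-sham difference by (g1 + g2)/4 in size: 0.125 to 0.5 Borg point for assumed equal drifts of 0.25 to 1, and half that over all eight patients, against an MCID of 1. The sign depends on whether active or sham is repeated. A W4 that replaces an invalid second visit keeps the order but leaves a bias of g2/4 in size, so that case is smaller and not free of bias.

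These sizes rest on W4 repeating the failed condition, on the target balance of two per sequence being reached, and on drift values that the article does not supply. The primary completion proportion is not biased by the reversal, and nothing here supports calling the crossover or the feasibility conclusion invalid.

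**What to change.** In Schedule of visits:
1. State that a repeat visit delivers the condition of the visit it replaces.
2. When a fault at the first experimental visit is known in time, repeat that visit before crossing over, and count the 1–2 week interval to visit 3 from the repeat.
3. Keep W4 for an invalid second experimental visit, or for a first-visit fault found only after visit 3.

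In Statistical analyses, or in the analysis plan: whenever W4 data are used, for either reason, code period by the actual order of the tests analysed, and show the exploratory contrasts with and without those data.

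The cost is a few sentences. Each repeat still uses the one extra visit already allowed. The downside is that visit 3 moves later for a patient whose first experimental visit is repeated.

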### Assignment of interventions

At visit 1, participants will be randomised, using randomisation function of REDCap, to one of four groups for subsequent study procedures: TENSac (visit 2 active → visit 3 sham) or TENSsa (visit 2 sham → visit 3 active), VNSac (visit 2 active → visit 3 sham) or VNSsa (visit 2 sham → visit 3 active), in a 1:1:1:1 ratio through the randomisation function of REDCap. A non-blinded investigator will run the randomisation and allocation process. Given our small sample size (n=8), no stratification will be applied for randomisation.

However, in a future randomised controlled trial, the randomisation should be minimised for FEV_1_ (<35% or ≥35% predicted), sex (one female participant (n=1) and one male participant (n=1), for a total of two participants per group arm (n=2) of the randomisation) and the number of severe exacerbations in the preceding 12 months (0 or ≥1 events).

### Statistical analyses

Descriptive analysis will be conducted for the primary objectives to evaluate the feasibility parameters. For the exploratory objective concerning the alteration in dyspnoea perception and pulmonary parameters, several statistical methods will be employed. The Borg slope will be analysed using a linear mixed model, which accounts for both fixed and random effects, allowing for the evaluation of changes over time within individuals. Paired sample t-tests will compare parameters with and without the interventions, determining if there is a significant difference. The χ^2^ test will assess the association between categorical variables.

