**Methods and analysis:**

We will conduct a feasibility cross-over trial in people with severe COPD and significant exertional dyspnoea referred for pulmonary rehabilitation. Patients will be recruited following the prerehabilitation assessment visit comprising a clinical evaluation and a maximal cardiopulmonary exercise testing on ergocycle. Subsequently, two study visits will be conducted within 2 weeks apart from each other. Eight participants will perform a submaximal constant work rate at 80% workload of the VO_2_ max, either with cervical tVNS (n=4) or trigeminal TENS (n=4). In a cross-over design, both patient groups will undergo sham and active treatment of the neuromodulation technique in a randomly assigned order. The main outcome will be feasibility, assessed by the percentage of patients who attend all visits and complete all tests. Secondary outcomes include other feasibility endpoints, the acceptability and suitability of the interventions (including an evaluation of sham as an exploratory outcome), and the incidence of adverse or undesirable events related to the procedures. Exploratory outcomes include changes in dyspnoea symptoms, measured using standardised questionnaires, such as Borg scale and the Visual Analogue Scale.

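### Active and sham are compared by paired t-tests that ignore period, so a possible shift from visit 2 to visit 3 widens the intervals or, if sequences become unbalanced, biases the contrast

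*Protocol article*

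**What the plan says.** All references are to the protocol article.

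- **Design.** Under Assignment of interventions, patients are randomised to four device-by-order groups "in a 1:1:1:1 ratio through the randomisation function of REDCap". Each patient has active stimulation at one of visits 2 and 3 and sham at the other. The figure 1 legend plans 1 to 2 weeks between these visits. The target is eight patients, four per device.
- **Analysis.** Under Statistical analyses: "Paired sample t-tests will compare parameters with and without the interventions, determining if there is a significant difference". The one other model for these outcomes concerns the Borg slope: "The Borg slope will be analysed using a linear mixed model, which accounts for both fixed and random effects".
- **Learning.** The strengths and limitations box says that the small sample and crossover design "introduce potential learning bias and limit the interpretation of the efficacy of the interventions". Schedule of visits offers the baseline test as the answer, "as it accounts for the effects of adaptation to the physical test (learning effect").
- **Training.** Also under Schedule of visits: "Study visits will be completed before starting or before completing the 12-week rehabilitation programme".
- **Incomplete pairs.** Under Participants, a patient with an exacerbation between the two experimental visits does not do the second one and may later be re-randomised and start again.

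**The concern.** A paired t-test treats the active-minus-sham differences as one sample with a common mean. In a two-period crossover that is true only if nothing changes between the periods except the treatment. Otherwise the change enters the difference with one sign in active-first patients and the opposite sign in sham-first patients. Randomising the order is what allows this change to be separated from treatment, and the paired t-test does not use that information.

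Here a change between visits is plausible. The main exploratory outcomes, maximum Borg score and pedalling time, come from an exercise test that is repeated within 1 to 2 weeks, possibly while the patient is in an exercise programme. The trial is meant to guide a larger one, which would naturally take from it the within-patient contrast and its variability. Both can be distorted by the stated test.

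**Working it through.** **Inputs from the article.** 8 patients, 4 per device; four groups at 1:1:1:1, so 2 per order within a device and 4:4 overall if exactly balanced; paired t-tests. The article gives no SD, effect size or period effect, so there is no figure of its own to reproduce.

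**Assumptions.** The SD of the within-patient difference d = active − sham is set to 1, and all results are in that unit. The period effect π (visit 3 minus visit 2) is varied over 0, 0.25, 0.5 and 1. Tests are two-sided at 5%.

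**Step 1: does the baseline remove the shift?** The exploratory outcomes are changes from baseline. With one baseline B for both visits, (Y_active − B) − (Y_sham − B) = Y_active − Y_sham. B cancels, so a change between visits 2 and 3 remains. This holds whatever the baseline test is. Schedule of visits describes it as a maximal CPET and later calls it a constant work rate test, but the argument does not depend on which is meant.

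**Step 2: bias.** With treatment effect τ, E[d] = τ − π in active-first patients and τ + π in sham-first patients. The mean of all differences therefore has

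bias = π × (n sham-first − n active-first) / n.

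| Active-first : sham-first | Bias |
|---|---|
| 4:4 overall, or 2:2 in a device | 0 |
| 3:5 overall | (5 − 3)/8 = 0.25 π |
| 1:3 in a device | (3 − 1)/4 = 0.50 π |
| 1:2 in a device (one patient lost) | (2 − 1)/3 = 0.33 π |

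**Step 3: precision when balanced.** The expected sample variance of d is 1 + π² × 4·n₁·n₂ / (n(n − 1)). At 4:4 the multiplier is 64/56 = 1.143. At π = 1 the reported SE is √(2.143/8) = 0.52, against a true SE of √(1/8) = 0.35. Simulation of 8 patients at 4:4 with devices pooled compared the paired t-test (7 df) with a period-adjusted comparison of d between the two orders (6 df):

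| π | Mean 95% CI width, paired | Adjusted | Power for a 1-SD effect, paired | Adjusted | Null rejection, paired |
|---|---|---|---|---|---|
| 0 | 1.61 | 1.66 | 68% | 66% | 5% |
| 0.25 | 1.67 | 1.66 | 65% | 66% | 4.4% |
| 0.5 | 1.83 | 1.66 | 58% | 66% | 3% |
| 1 | 2.38 | 1.66 | 34% | 66% | 0.7% |

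Null rejection with adjustment is 5% throughout. The two methods break even near π = 0.25.

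**Step 4: cost of adjusting, by device, if there is no period effect.** Each device has 4 patients at 2:2, so the SE is 0.50. Mean width is 2 × t × E[s] × 0.50:

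| Analysis | df | Mean width |
|---|---|---|
| Variance pooled over 8, no period term | 6 | 2.35 |
| Variance pooled over 8, common period term | 5 | 2.45 |
| One device alone, paired t-test | 3 | 2.93 |
| One device alone, period-adjusted | 2 | 3.81 |

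Like for like, the period term costs 2.45/2.35, about 4%, in the pooled model, and 3.81/2.93, about 30%, when a device is adjusted on its own.

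**The case against.** The strongest reply concerns weight. The affected comparisons are exploratory, the primary analysis is descriptive, and the article says that the trial is not designed to determine efficacy and will probably not allow a conclusion on it. Under the planned 1:1:1:1 allocation the estimate is unbiased and the test errs on the cautious side. The interval between visits is kept short to limit outside influences. If the period effect is small, nothing is gained: at zero the paired test is slightly better, and at 0.25 SD the two are nearly equal. All of this stands. It limits the importance of the point but does not make the stated test right for the design.

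A reader might infer three stronger things that the document does not support.

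- **That a period effect is expected.** Learning bias is called potential, and training between the visits is allowed, not required. The 1-SD row is one assumed value, not a forecast.
- **That the Borg-slope model also omits period.** The article says that this model has fixed and random effects and does not list them. That detail may sit in a fuller plan.
- **That rehabilitation attendance between visits goes unrecorded.** The collected variables are listed in supplementary tables that are not shown.

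Nor does the point need the allocation to be unblocked. The article does not describe blocking, and drop-out or a restart is enough to unbalance groups of two.

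**Conclusion.** The point holds as a limited one. The article names a specific test that leaves out period in a randomised-order crossover, gives its own reasons why a shift between visits is possible, and relies on a baseline that cancels out of the contrast.

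The bias fractions follow from algebra and need no assumed values: zero when sequences are balanced, 0.25 of the period effect at 3:5 overall, and 0.5 at 1:3 within a device. The loss of precision depends on an unknown period effect. It is negligible at 0.25 SD, about 10% of CI width at 0.5 SD (1.83/1.66) and about 43% at 1 SD (2.38/1.66), with devices pooled at 4:4. It would be wrong to conclude that the planned contrast is biased as designed: bias requires realised imbalance, which drop-out or re-randomisation after an exacerbation makes possible but not certain. The primary feasibility outcome is untouched.

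**What to change.** Replace the paired t-tests with one crossover model over all 8 patients: patient, period, and a treatment effect for each device, with the period effect and residual variance common to both devices. The equivalent is a regression of the within-patient differences on device and order. Report each active-minus-sham estimate with its 95% CI and drop the wording about determining a significant difference.

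Do not adjust each device of four separately: with no period effect that widens the interval from 2.93 to 3.81 SD.

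The cost is a change of analysis wording, one degree of freedom, and the assumption that both devices share a period effect and a residual variance, which should be stated. If there is no period effect, the price is about 3% of CI width for the pooled contrast (1.66 versus 1.61) and about 4% for a device-specific one (2.45 versus 2.35). No patient, visit or measurement is added.
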